### Statistical and analytical plan

#### Sample size calculation

This is an exploratory study, aimed at rectifying the current lack of information on the use of CP to treat MERS-CoV infection. Due to the exploratory nature of this study and the paucity of sequential data on viral RNA levels in respiratory tract and blood samples from MERS-CoV-infected patients, and on their clinical progress, the sample size is fixed at 20, which is a realistic target for a study of 12 months duration. The sample size of 20 is sufficient to reach a conclusion that the 28-day survival rate significantly exceeds 60 % (p = 0.032, 2-sided) if 17 or more patients survive for the 28 days of follow-up. This would represent promising evidence to motivate a full-scale comparative clinical trial.

### Statistical analyses

#### Analysis of viral load data

Serial MERS-CoV viral load measurements will be displayed as box and whisker plots for the 20 treated patients against time.The probability of a patient having an undetectable viral load from all sampled sites by day 3 after administration of therapy will be estimated by the proportion of the 20 treated patients for whom this occurs. An exact, conservative, two-sided confidence interval for this probability will be calculated using the method of Clopper and Pearson (1934).The relationship between log viral load at day 3 and the neutralizing antibody dose received will be characterised by fitting a regression model to the data from the 20 treated patients. The log viral load at baseline will be included in this model.The relationship between the probability of a patient having an undetectable viral load by day 3 and the neutralizing antibody dose received will be characterised by fitting a log-logistic regression model to the data from the 20 treated patients. The log viral load at baseline will be included in this model.

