#### CP therapy phase

We will screen consecutive critically ill patients admitted to the intensive care unit or other areas of the hospital where critically ill patients receive care for the following criteria:

Inclusion criteriaCritical illness as defined by one or more of the following: admission to an ICU; current receipt of mechanical invasive or non-invasive ventilation; partial pressure of oxygen to fraction of inspired oxygen ratio (PaO2:FiO2) of <300 mmHg; current receipt of intravenous vasoactive medications to maintain mean arterial pressure >65 mmHg; new-onset (since development of MERS-CoV symptoms) receipt of renal replacement therapy or extra-corporeal life support.Laboratory-confirmed MERS-CoV infection (by real-time reverse-transcription polymerase chain reaction rRT-PCR).Age of more than or equal to 14 years.

Exclusion criteriaSymptomatic illness exceeding two weeks (14 days) at time of enrollment.Negative rRT-PCR from respiratory secretions or blood within 48 h prior to assessment of eligibility.History of allergic reaction to blood or plasma products (as judged by the investigator).Known IgA deficiency.Medical conditions in which receipt of 500 mL intravascular volume may be detrimental to the patient (e.g., actively decompensated congestive heart failure).

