#### CP therapy phase

We will establish safety of the study intervention, as measured by number of serious adverse events related to study intervention (adverse events include development of complications of intravascular volume overload and clinical pulmonary edema by temporally related-shortness of breath, chest radiograph findings and change in oxygenation requirements; development of transfusion-related acute lung injury (TRALI) or substantial allergy or anaphylaxis). These serious events will be adjudicated by a committee of 3 investigators.*Clinical Outcomes* We will measure (1) sequential organ failure assessment (SOFA) scores on study days 1, 3, 5, 7, 14, and 28 (2) requirement for organ support (oxygen and ventilation; dialysis; vasopressors) after enrollment; (3) length of stay in ICU defined as the number of calendar days between admission and final discharge from ICU for the same ICU admission of enrollment; and duration of mechanical ventilation, defined as the number of calendar days between start and final liberation from mechanical ventilation for the same ICU admission of enrollment and hospital length of stay as defined as the number of calendar days between admission to hospital and final discharge from hospital for the same hospital admission; and (4) vital outcome (mortality) in ICU, hospital and at 28 days.Other clinical outcomes include “ICU-free days”, defined as the number of days that patients are not in ICU in the first 28 days after enrollment. Patients who die within 28 days will be counted separately, and not categorised by ICU-free days. Similarly, “ventilator-free days” is defined as the number of days that patients do not receive mechanical ventilation in the first 28 days after enrollment. “Renal replacement therapy-free days” and “vasopressor-free days” are defined in a similar way. Serial chest radiograph findings, as obtained by the clinical team will also be recording as per case report form, graded as unilateral or bilateral infiltrates, in 1–4 quadrants.*Laboratory Outcomes* We will measure the following laboratory outcomes:The serum level of anti-MERS-CoV antibodies before and after administration of CP.MERS-CoV viral load (the primary laboratory outcome is viral clearance from all sampled sites by day 3 after administration of CP).

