### Stratified analyses

We will conduct exploratory stratified analyes based on (1) the time between symptom onset and CP therapy initiation, (2) comorbidities, (3) co-intervention; and (4) baseline severity (SOFA scores) at treatment initiation.

The SAS System for Windows version 9.3 (SAS Institute, Inc., Cary, North Carolina) and R will be used for all analyses.

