### Discussion and current status

This protocol was developed collaboratively by King Abdullah International Medical Research Center (KAIMRC), Gulf Cooperation Council (GCC) Infection Control Center Group and the World Health Organization—International Severe Acute Respiratory and Emerging Infection Consortium (ISARIC-WHO) MERS-CoV Working Group. It was approved by the Ministry of the National Guard Health Affairs Institutional Review Board (IRB) (approval number IRBC/13/244, 5th June 18, 2014) and has been registered at clinicaltrials.gov (NCT02190799).

If proven effective, CP therapy is an attractive therapeutic option for MERS-CoV infection. Besides the biologic plausibility of this therapy, it is easy to obtain and administer, relatively inexpensive, and is likely to be acceptable to patients and treating teams. Side effects are unlikely to differ from those of transfusion of any other fresh frozen plasma. We believe this study protocol sets the stage to a large efficacy trial.

The strengths and weaknesses of the study protocol should be noted. In the CP collection phase subjects will be enrolled from 4 different cohorts, in order to explore all potential donors. It is unknown, at this point, which subjects are likely to have high antibody titers and therefore be CP donors. We are hoping that this feasibility study will help identifying a group of superdonors who have very high titers. By identifying the characteristics of such individuals, a more focused approach for donation can be followed. The CP therapy phase is not designed to establish efficacy; such objective requires an adequately powered randomized controlled trial. However, we believe performing this feasibility study is an essential step to examine the safety, clinical and laboratory effects and the pharmacokinetics of the MERS-CoV antibody response. The study involves giving critically ill patients this therapy in a controlled monitored setting. However, a recent systematic review suggested that early treatment with CP is likely to be more effective than late treatment (Mair-Jenkins et al. 2015). Therefore, if the feasibility study shows that CP is safe and feasible, the next step should be a randomized controlled trial that is sufficiently powered to detect effect on mortality and enrolls patients early in the course of the disease.

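### The dose-response models leave out the recipient's own pre-infusion antibody, which the trial measures: a loss of precision, and exposure to any link between dose and recipient titre

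*Protocol article*

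**What the plan says.** All references are to the protocol article.

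- **Entry.** Under Study population, CP therapy phase, patients are excluded only once symptoms have lasted more than 14 days. The exclusion that bears on the state of the infection is virological: "Negative rRT-PCR from respiratory secretions or blood within 48 h prior to assessment of eligibility". There is no criterion on the recipient's antibody.
- **Measurement.** The laboratory outcomes include "The serum level of anti-MERS-CoV antibodies before and after administration of CP". Laboratory procedures applies ELISA and then IFA to both donor and participant serum, with IFA reactive from 1:10. Follow-up includes baseline and 30 minutes after the second unit.
- **Models.** Under Analysis of viral load data, "The relationship between log viral load at day 3 and the neutralizing antibody dose received will be characterised by fitting a regression model", and then "The log viral load at baseline will be included in this model". The log-logistic model for undetectable virus carries the same single covariate. So do the logistic models for SOFA and organ support and the Cox model for death, under Analysis of clinical data.
- **Strata.** The exploratory list is "1) the time between symptom onset and CP therapy initiation, (2) comorbidities, (3) co-intervention; and (4) baseline severity (SOFA scores) at treatment initiation". Recipient antibody is not on it.
- **Source of dose.** The Background expects plasma from different survivors to differ in neutralizing antibody. Each patient gets 2 units, and the only stated matching rule is ABO compatibility. Dose is not randomised.
- **Size.** "the sample size is fixed at 20, which is a realistic target for a study of 12 months duration".

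**The concern.** The dose-response analysis is a main reason for the study: the Background and Conclusions say it should guide the antibody dose for a later randomised trial. The recipient's own level of the same antibody is an obvious prognostic variable for viral clearance. The protocol itself expects infection to produce antibody, since it recruits recovering patients as donors. A recipient who is already seropositive may clear virus largely regardless of the plasma given.

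The article names the covariate model by model, so this is a stated choice and not a detail lost in condensing. In 20 patients, leaving out a strong predictor makes an imprecise slope more so, and leaves the slope exposed if dose and recipient titre happen to be related. For the antibody outcome, later samples contain both infused antibody and the patient's own.

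**Working it through.** **The plan's own figure.** There is no figure for the dose models. The one sample size figure is that "the 28-day survival rate significantly exceeds 60 % (p = 0.032, 2-sided) if 17 or more patients survive". It reproduces: P(X ≥ 17 | n = 20, 0.60) = 0.01596, and doubled this is 0.0319. It matters here only because it fixes n and shows how few deaths there may be: 20 − 17 = 3 at that threshold, and 20 × 0.40 = 8 at 60% survival.

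**Inputs.** From the protocol: n = 20; dose plus baseline log viral load in each model. Assumed, because the documents give no seroconversion rate or titre effect: a linear model for day-3 log load; standardised normal predictors; titre explaining R² = 10%, 30% or 50% of the variance left after baseline load; dose-titre correlation r = 0 or ±0.3.

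1. **Precision when r = 0.** With p random normal predictors, the slope variance is residual variance / (n − p − 2).
   - Without titre (p = 2): √(1/16) = 0.25.
   - With titre (p = 3): R² = 10%, √(0.9/15) = 0.245; 30%, √(0.7/15) = 0.216; 50%, √(0.5/15) = 0.183.
   - The SD falls by about 2%, 14% and 27%.
   - The sample needed to match this without titre solves 1/(n − 4) = (1 − R²)/15. It gives n = 20.7, 25.4 and 34, or under 1, about 5 and 14 extra patients.

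2. **Bias when r = 0.** A simulation at n = 20 used a true dose slope of −0.5, titre slope −0.5 or −1.0, viral-load slope 0.7, residual SD 1, and titre-load correlation 0 or −0.5. The mean slope without titre was −0.49 to −0.50, so there was no bias. Its SD was 0.27 to 0.35, against about 0.26 with titre.

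3. **Shift when r = ±0.3.** The slope without titre moves by r√R², in SD units of the remaining outcome variation: 0.3 × √0.1 = 0.09; 0.3 × √0.3 = 0.16; 0.3 × √0.5 = 0.21. In the same simulation the mean slope became −0.61 to −0.80 at +0.3 and −0.20 to −0.39 at −0.3. Adding titre restored −0.50 each time. The smaller shifts occurred where baseline load was correlated with titre.

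4. **Chance correlation.** For two independent variables at n = 20 the SD of r is 1/√19 = 0.23. By simulation the median |r| is 0.16 and the 95th percentile 0.44.

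5. **Logistic models.** In a large-sample simulation with dose independent of titre, a true dose log-odds of 0.70 was attenuated to 0.67, 0.59 and 0.50 for titre log-odds of 0.5, 1.0 and 1.5.

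6. **Cost of adding the term to sparse models.** Logistic simulation: n = 20, independent standardised covariates, viral-load log-odds 0.7, titre log-odds 1.0, dose effect zero. Separation (no finite estimate) rises from about 2–3% to 19% with 3 events, and from under 1% to about 7% with 5. With 8 events it reaches about 3%.

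**The case against.** The strongest counter-argument is that dose is a property of the donor plasma. Nothing in the protocol ties it to the recipient's titre, and the linear slope is then unbiased. This stands. A reader might infer that the donor effect is necessarily mixed with natural seroconversion in every dose slope; the documents do not support that. Chance imbalance is also already part of the slope's sampling error, so it must not be counted once as lost precision and again as bias. Only a systematic link would be bias, and the protocol neither states nor rules one out.

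Second, time from symptom onset heads the stratified list and is a reasonable proxy for seroconversion, and baseline viral load may carry part of the same information. Both reduce the gap. Neither replaces the measured value, and the strata are exploratory, not model adjustment.

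Third, a reader might infer that late antibody rises will be credited to the plasma. No section says so. The stated aim is "the pharmacokinetics of the MERS-CoV antibody response", which can be read as total antibody in the patient. What remains is a request for clear labelling.

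Fourth, one covariate for 20 patients in a study that calls itself exploratory is defensible parsimony, and a blanket extra term could make the sparse models inestimable. This stands and limits the fix. So does the point that IFA follows a screening ELISA: some recipients may have no IFA titre, and a value below 1:10 has no logarithm without a rule.

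**Conclusion.** The point holds in a limited form. The trial collects the recipient's pre-infusion antibody, the baseline variable closest to the treatment under study, but uses it in none of the five dose-response models and not in the strata.

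If dose is independent of titre, the consequence is lost precision in the day-3 log viral load slope (SD 0.25 against about 0.22 at an assumed R² of 30% and 0.18 at 50%; negligible at 10%) and attenuated logistic effects. A shift of about 0.1 to 0.2 SD needs a dose-titre correlation, here assumed at 0.3. All these sizes rest on assumed effects.

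Adjustment would not rescue the uncontrolled day-3 clearance proportion, to which the patient's own antibody contributes whatever model is fitted. The study's validity as a pilot is not in question.

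**What to change.** - **Day-3 log viral load model:** add recipient pre-infusion antibody beside baseline log viral load. Use either the ELISA OD ratio or log IFA titre, with a stated value for samples below 1:10.
- **Stratified analyses:** add baseline serostatus (for example IFA below 1:10 against 1:10 or above, the protocol's own reactive cut-off).
- **Log-logistic, logistic and Cox models:** use the term only in a prespecified sensitivity analysis, and only if event numbers allow.
- **Antibody levels:** report the rise from baseline to 30 minutes after the second unit as the passive increment, and later levels as combined passive and own antibody.

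The cost is one degree of freedom in the linear model and a short rule for non-reactive samples. Baseline antibody measurement is already planned. If the log IFA titre is chosen, IFA must be run on all baseline samples, including ELISA-negative ones; the OD ratio avoids this. The risk is separation if the term is forced into models with few events.

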#### Analysis of clinical data

The SOFA score and indicators of whether the patient requires organ support via oxygen and ventilation, dialysis or vasopressors will be plotted against time.The relationships between the SOFA score at day 3 and the neutralizing antibody dose received, and between receipt of any type of organ support during the 28 days of observation and the neutralizing antibody dose received, will be characterised by fitting a logistic regression model to the data from the 20 treated patients. The log viral load at baseline will be included in these models.The vital status (alive or dead) of each patient will be recorded for all days 0–28. The proportion alive will be plotted against time.The relationship between the hazard of death and the neutralizing antibody dose received will be characterised by fitting a Cox proportional hazards regression model to the data from the 20 treated patients. The log viral load at baseline will be included in this model.The probability of a patient dying on or before 28 days will be estimated by the proportion of the 20 treated patients for whom this occurs. An exact, conservative, two-sided confidence interval for this probability will be calculated using the method of Clopper and Pearson (1934).The time from infection/exposure and sample collection in days, duration from infection/exposure to CP therapy, length of stay in ICU; the number of ICU-free days; the duration of mechanical ventilation; the numbers of ventilator-free days, of renal replacement therapy-free days, and of vasopressor-free days; and the length of stay in hospital will be presented as histograms, and suitable summary statistics will be computed.

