#### Frequency and duration of follow-up

Clinical and laboratory data will be collected at baseline, 30 min after first dose, 30 min after second dose, study days 1, 3, 5, 7, 14, and 28.

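### One logistic regression is named for both the day-3 SOFA score and a yes/no organ-support outcome, with no cut-point or ordinal form for SOFA and no adjustment for baseline SOFA

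*Protocol article*

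**What the plan says.** In the protocol article, Analysis of clinical data, one sentence names two outcomes: "The relationships between the SOFA score at day 3 and the neutralizing antibody dose received", and the relation "between receipt of any type of organ support during the 28 days of observation and the neutralizing antibody dose received". Both, it says, "will be characterised by fitting a logistic regression model to the data from the 20 treated patients". The next sentence sets the adjustment: "The log viral load at baseline will be included in these models". No other covariate is named.

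Under Outcome measures, SOFA is listed as a score on study days 1, 3, 5, 7, 14 and 28. It is not defined there or elsewhere as an event or a threshold.

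Three other places bear on the point:

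- Analysis of viral load data: "The relationship between log viral load at day 3 and the neutralizing antibody dose received will be characterised by fitting a regression model". That model is not called logistic, and it includes the baseline value of the same quantity.
- Frequency and duration of follow-up: "Clinical and laboratory data will be collected at baseline".
- Stratified analyses: one of the four factors is "baseline severity (SOFA scores) at treatment initiation".

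**The concern.** The two outcomes in the sentence are of different types. Any organ support within 28 days is yes/no, and binary logistic regression fits it. SOFA at day 3 is a score with many levels, and the same model cannot be fitted to it until someone decides how to cut it. The article gives no cut. One chosen after 20 scores have been seen is open to selection, and any cut throws away the differences between patients on the same side of it.

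The second part is adjustment. A patient's SOFA on day 3 can be expected to depend in part on SOFA at infusion. Leaving baseline SOFA out leaves that variation in the error term and widens the interval for the dose slope.

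The background section gives the relation between neutralising antibody dose and clinical and laboratory features as a reason for the study, meant to help choose the dose or dosing range for a later randomised trial. Day-3 SOFA is one of the few clinical dose-response analyses named. A weak or undefined version of it gives that trial less to work with.

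**Working it through.** **Plan's own figure.** The article states no power, SD or correlation for the SOFA model, so there is nothing to reproduce for it. Its one statistical figure, p = 0.032 for 17 of 20 survivors against 60%, is correct: P(X ≥ 17 | n = 20, p = 0.6) = 0.01596, and 2 × 0.01596 = 0.0319. It does not bear on this point.

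**Step 1: compare the paired analyses.**

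| Outcome | Type | Model named | Adjusted for |
|---|---|---|---|
| Log viral load, day 3 | continuous | regression | its own baseline |
| Undetectable viral load by day 3 | yes/no | log-logistic regression on a probability | log baseline viral load |
| SOFA, day 3 | multi-level score | logistic regression | log baseline viral load |
| Any organ support, 28 days | yes/no | logistic regression | log baseline viral load |

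The viral-load section separates the continuous from the binary outcome and gives each a model of its type. The clinical section merges them. The SOFA row is the only one where outcome and model do not match on a plain reading. It is also a day-3 measurement that, unlike log viral load, is not adjusted for its own baseline.

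**Step 2: what baseline adjustment can gain.** Let r be the correlation between baseline and day-3 SOFA. If dose is unrelated to baseline SOFA and baseline viral load carries no information on SOFA (both assumptions), replacing viral load by baseline SOFA multiplies the residual SD by √(1 − r²), with the same number of covariates:

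- r = 0.3: √(1 − 0.09) = 0.954, an interval for the dose slope about 5% narrower
- r = 0.5: √(1 − 0.25) = 0.866, about 13% narrower
- r = 0.7: √(1 − 0.49) = 0.714, about 29% narrower

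**Step 3: power, by simulation.** Assumptions, none of them from the document: n = 20, SOFA SD 3.5, scores rounded and clipped to 0–24, true effect −1.5 points per SD of dose, no deaths before day 3.

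| r | Linear, with baseline SOFA | Linear, viral load only |
|---|---|---|
| 0.3 | 41% | 38% |
| 0.5 | 48% | 38% |
| 0.7 | 65% | 40% |

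**Step 4: cost of dichotomising.** At r = 0.7 with the same SD and effect, a median-split logistic model with viral load had 34% power, against 40% for the linear model with the same covariate, a loss of 6 points. With no dose effect, its likelihood-ratio test rejected in 6.9% of runs at nominal 5%; the linear models rejected in 4.2% (viral load) and 5.4% (baseline SOFA).

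A second simulation (SD 4, effect 0.5 SD, r from 0.3 to 0.9) gave 38–42% for the split and 49–50% for the linear model, both without baseline SOFA. The split rejected in 7–8% of null runs. The direction is the same.

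**Step 5: early deaths.** The figures in Step 3 have no deaths. At r = 0.7, entering SOFA 24 for the two sickest patients in least squares cut power with baseline SOFA from 65% to 51%. Entering it for two patients unrelated to severity cut it to 20%.

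**The case against.** The text says logistic, not binary logistic. A proportional-odds model is an ordinal logistic regression and would suit a score, so the sentence can be read in a way that runs. The article is also a condensed account, and the Steering Committee is to formulate the analysis plan. This stands in part: the ordinal reading is possible. It is strained, though, because one model is named for a score and a yes/no indicator together, and nothing in the text mentions ordered categories. Nor is this only detail left for later. A model is named, and on its plain reading it does not fit one of its two outcomes.

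The power gain depends on r, which the document does not give. This stands. At r = 0.3 the gain is 3 points (41% v 38%), and the 65% at r = 0.7 should not be quoted alone or without the condition of no early deaths.

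The analysis only characterises a relationship in a study described as exploratory and not designed to establish efficacy. No stated decision hangs on it. This also stands and limits the severity.

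Three stronger readings are tempting, and the document does not support them:

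- A reader might infer that the dose effect on SOFA is confounded by severity. Every patient receives two units; dose varies through donor antibody level, and plasma must be ABO compatible. Nothing says that sicker patients get more or less antibody. Chance correlation between dose and baseline SOFA has an SD of about 1/√19 = 0.23 at n = 20, but that is a matter of precision: the linear model without baseline SOFA kept its type I error (4.2%).
- A reader might infer that the omitted covariate explains most of day-3 SOFA. No correlation is given, and more than half of the variance is explained only if r exceeds about 0.71 (0.7² = 49%).
- A reader might infer that baseline SOFA is discarded. It is omitted from this model but kept as a factor for the stratified analyses. Strata among 20 patients are a weak substitute for adjustment, but the measurement is used.

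**Conclusion.** The point holds in limited form. The article names one logistic model for a multi-level score and a binary outcome. On the plain, binary reading, the SOFA analysis needs a cut-point that is not stated, and dichotomising 20 patients loses information. The model also leaves out baseline SOFA, in contrast to the article's own treatment of day-3 viral load.

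Under the assumptions of Step 3, dichotomising costs about 6 points of power at r = 0.7 (40% to 34%). Omitting baseline SOFA from a linear model costs about 3 points at r = 0.3, 10 at r = 0.5 and 25 at r = 0.7. The SD, effect size, correlation and score range are all assumed, and the figures exclude early deaths. The direction is firm; the size is not.

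Severity is moderate to low. This is one exploratory analysis in a single-arm study of 20 patients, and neither the feasibility and safety aims nor the primary laboratory outcome depends on it.

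**What to change.** Split the sentence in two.

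1. **SOFA at day 3:** relate the score to antibody dose with a proportional-odds model (or a linear one) that includes baseline SOFA, and name the form in the text.
2. **Deaths before day 3:** place them in the worst ordinal category, or give them the worst rank. Do not enter SOFA 24 in a least-squares fit, where one or two such values can dominate 20 observations (Step 5). This favours the proportional-odds form.
3. **Organ support:** keep binary logistic regression, and call it binary.

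The cost is wording. Clinical data are collected at baseline, and SOFA at treatment initiation is already needed for the stratified analyses. The SOFA schedule under Outcome measures starts at day 1, so it is worth adding baseline there.

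The downside is that 20 patients may not support dose, baseline SOFA and baseline viral load in one model. Baseline SOFA may then have to replace baseline viral load here, and this model would no longer share its covariate with the other dose models. That choice should be made before the data are seen.

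### The logistic dose model for any organ support over 28 days rests on an outcome nearly every patient is likely to have, so it will probably say little about antibody dose

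*Protocol article*

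**What the plan says.** **Model.** Under Analysis of clinical data, the protocol article plans to relate antibody dose to day-3 SOFA score and, separately, to organ support. The second relationship is "between receipt of any type of organ support during the 28 days of observation and the neutralizing antibody dose received". It "will be characterised by fitting a logistic regression model to the data from the 20 treated patients", with baseline log viral load as a covariate. Under Sample size calculation, "the sample size is fixed at 20".

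**Outcome.** Under Outcome measures, CP therapy phase, the clinical outcome is "requirement for organ support (oxygen and ventilation; dialysis; vasopressors) after enrollment". The analysis section names the same three kinds of support.

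**Entry.** Under Study population, CP therapy phase, a patient must be critically ill by at least one of five criteria. ICU admission is the first. The second is "current receipt of mechanical invasive or non-invasive ventilation". The third is a low oxygenation ratio (PaO2:FiO2 below 300 mmHg), the fourth is treatment with vasoactive drugs, and the fifth is new-onset "receipt of renal replacement therapy or extra-corporeal life support".

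**The concern.** The entry condition and the outcome overlap heavily. A patient who qualifies through ventilation, vasoactive drugs or renal or extracorporeal support is already receiving support, and is a yes as soon as it continues past enrolment. Nothing in the text restricts the outcome to new support.

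Two things follow. First, an outcome that is nearly constant in 20 patients leaves a logistic model little or nothing from which to estimate a dose slope. Second, for patients on support at entry the result is essentially fixed before plasma is given, so dose cannot change it. Even with several patients free of support, the coefficient would largely reflect who entered without support rather than any response to dose.

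The Background gives the link between antibody dose and clinical and laboratory effects as a reason for running this small open-label study, so that it can guide dose selection for a later randomised trial. The protocol states three clinical dose models (SOFA, organ support, hazard of death), and this is one of them.

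**Working it through.** **Plan's own figures.** The protocol gives no expected rate of organ support, so there is no figure to reproduce for this model. The one computed figure in the sample-size section, p = 0.032 for 17 or more survivors of 20 against 60%, does reproduce: the exact upper tail is 0.01596, and 2 × 0.01596 = 0.0319. It does not bear on this point.

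**Step 1: entry criteria against the outcome definition.**

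| Entry criterion | Organ support under the outcome definition? |
|---|---|
| Invasive or non-invasive ventilation | Yes, directly |
| Intravenous vasoactive drugs | Yes, directly |
| New renal replacement or extracorporeal support | Yes, or practically so |
| PaO2:FiO2 below 300 mmHg | On room air this is PaO2 below 300 × 0.21 = 63 mmHg, so oxygen is practically implied |
| ICU admission alone | Not necessarily |

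Only the last route can bring in a patient without support, and that patient must then need none for 28 days to be a no.

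**Step 2: how many patients could be a no.** Let p be the probability that a patient has any support in 28 days. This is an assumption, shown as a range. With n = 20 independent patients:

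- P(all yes) = p^20
- P(at most one no) = p^20 + 20 × (1 − p) × p^19
- Expected number of no = 20 × (1 − p)

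| p | Expected no | P(all 20 yes) | P(at most one no) |
|---|---|---|---|
| 80% | 4 | 0.012 | 0.069 |
| 85% | 3 | 0.039 | 0.176 |
| 90% | 2 | 0.122 | 0.392 |
| 95% | 1 | 0.358 | 0.736 |
| 98% | 0.4 | 0.668 | 0.940 |
| 99% | 0.2 | 0.818 | 0.983 |

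**Step 3: when the fit does not exist.** A maximum-likelihood logistic fit has no finite estimate if all outcomes are equal or if the covariates separate yes from no. Separation was checked by linear programming in 1,500 simulated data sets per setting, with 20 patients, two independent standard normal covariates and no true effect. With exactly one no, the data separated in about 33% of simulations; with two, about 6%; with three, about 2%. Overall, the fit did not exist in 4%, 11%, 24%, 51%, 76% and 87% of data sets at p = 80%, 85%, 90%, 95%, 98% and 99%.

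Cross-check at 95%: all yes 0.358, plus one no 0.377 × 0.333 = 0.126, plus two no 0.189 × 0.061 = 0.012, total 0.496. This agrees with the simulated 0.51 within simulation error.

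**Step 4: when the fit does exist.** The model has two slopes, dose and baseline log viral load. One or two no outcomes give 1/2 = 0.5 or 2/2 = 1 outcome in the rarer class per slope. An estimate on that basis carries almost no information about dose.

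**The case against.** A reader might infer that the model simply cannot be estimated. The documents do not support that. It is literally true only if all 20 are yes or the data separate. The rate is assumed, and at 95% there is a 1 − 0.358 = 64% chance that at least one patient is a no. At 80% to 85% a fit would usually exist.

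The near-universal yes also depends on a reading. The outcome section speaks of support after enrolment without saying whether continuing support counts, and it writes oxygen and ventilation as a single item. If only ventilation counts, the rate falls. ICU admission alone also qualifies a patient. These points stand and limit the certainty. They do not remove the overlap for patients who enter on ventilation, vasoactive drugs or renal support.

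A second stronger inference is that the study's purpose is defeated. That does not hold either. The sample-size section calls the study exploratory and the Discussion says it is not designed to establish efficacy. This is one of five dose models across the viral and clinical analyses. Safety, feasibility, day-3 viral clearance and the survival benchmark do not depend on it. Organ support is still plotted over time, and support-free days are still summarised.

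Finally, exact or penalised fallbacks and detailed coding of the indicator commonly belong in an analysis plan, which is not shown, so their absence is not held against this text. What the protocol itself fixes is the outcome, window, model, covariate and sample, and that combination discriminates poorly in this population.

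**Conclusion.** The point holds in a limited form. The stated model will probably be uninformative about dose and may have no finite estimate. This rests on three assumptions: support continuing from entry counts, oxygen alone counts, and few patients enter on ICU admission without support. Under them a rate of 95% or more is plausible, though the documents do not state one, and at 95% to 99% the chance of at most one patient without support is 74% to 98%. If the assumptions fail, the rate is lower and the problem milder, but for patients already supported at entry the outcome would still be largely settled before treatment.

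The consequence is the loss of one exploratory dose-response analysis. It should be fixed, and it does not undermine the trial.

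**What to change.** In Analysis of clinical data, replace the binary outcome with one that varies among critically ill patients and is already defined under Outcome measures: ventilator-free, vasopressor-free and renal-replacement-free days to day 28. Regress it on dose and baseline log viral load with an ordinal or rank-based model, with death by day 28 as the worst category.

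State how this fits the existing definition, which counts deaths separately from ICU-free days and defines the other free-day outcomes along similar lines. Ranking death lowest for this model adds to that definition, so it needs explicit wording. A composite that includes oxygen-free days is best avoided unless daily oxygen status is recorded: the follow-up section lists days 1, 3, 5, 7, 14 and 28, and daily oxygen data are not stated to be captured.

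The cost is one added outcome definition, and precision will remain limited with 20 patients. Modelling new support of a type absent at baseline is a weaker alternative, because it leaves fewer than 20 patients per type and may itself be sparse.
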